## Abstract

**Background:**

Interprofessional education in childhood cancer is a multifaceted field involving multiple healthcare professionals with general and specialised knowledge and skills. Complex treatment, care and rehabilitation require continuous professional development and maintenance of healthcare professionals’ competencies in their field of expertise. However, limited knowledge exists in comparing interprofessional and monoprofessional education. Only a few randomised studies have evaluated the effectiveness and efficiency of interprofessional education.

The objective of this single-centre, investigator-initiated cluster randomised trial is to study the effect of interprofessional versus monoprofessional case-based learning on healthcare professionals’ knowledge of gastrointestinal side effects and attitudes towards team collaboration.

**Methods:**

This study will randomise healthcare professionals to participate in either the experimental interprofessional group or the control monoprofessional group of case-based learning. The topic of the case-based intervention will be gastrointestinal side effects, one of six categories identified in a three-round Scandinavian Delphi study as relevant for interprofessional education in childhood cancer.

The primary outcome is the self-reported questionnaire Assessment of Interprofessional Team Collaboration Scale. Secondary outcomes are measured by the self-reported questionnaires Readiness for Interprofessional Learning Scale Questionnaire, Safety Attitudes Questionnaire, and knowledge will be evaluated using a multiple-choice quiz.

Participants will receive the self-reported questionnaires about 2 weeks before and 1 month after the intervention. On the day of the intervention, participants will answer a multiple-choice quiz before and after the case-based learning.

Linear mixed models will be used to compare differences between the two groups in mean scores postintervention, adjusting for preintervention scores.

**Discussion:**

This study will provide insight into the differences between interprofessional and monoprofessional case-based learning and how it affects healthcare professionals’ knowledge of gastrointestinal side effects and attitudes towards team collaboration.

**Trial registration:**

The intervention was registered at Clinical Trials.gov: NCT04204109 on December 102,019 and with the National Committee on Health Research Ethics: H-19087506 December 112,019 and the Danish Data Protection Agency: P-2019-637 October 152,019.

**Supplementary Information:**

The online version contains supplementary material available at 10.1186/s12913-020-05980-2.

## Background

Interprofessional education in childhood cancer is a multifaceted field involving multiple healthcare professionals with general and specific knowledge and skills. Complex treatment, care and rehabilitation require continuous professional development and maintenance of healthcare professionals’ competencies in their field of expertise to provide children and adolescents with cancer and their families the best possible treatment and care [1].

There has been a shift in the treatment paradigm in childhood cancer from cure towards normality and interprofessional collaboration in childhood cancer research has contributed to this [2, 3]. Four out of five children with cancer will survive [4], but half of all children with acute lymphoblastic leukaemia are still affected by at least one of 14 severe toxic, treatment-related side effects [5]. Moreover, the burden of mortality in childhood cancer survivors is high and continues in adulthood [6].

To continuously ensure and strengthen high-quality treatment and care, interprofessional education must be strategically planned based on a curriculum involving all relevant healthcare professionals and specific learning outcomes [7]. This necessitates a curriculum framework comprising problem identification, needs assessment, aims and objectives, educational strategies, implementation, assessment and evaluation, and feedback [7].

In a scoping review, we described a lack of well-structured and evaluated interprofessional education programmes [8]. Postgraduate education at the department of paediatric oncology, Rigshospitalet, University of Copenhagen is organised monoprofessionally, with no formal curriculum for ensuring delivery of safe, high-quality interprofessional healthcare to this group of children, adolescents and their families.

In a three-round Scandinavian Delphi study to establish consensus on learning objectives for an interprofessional education programme in childhood cancer [9], 30 designated experts from 12 out of 14 childhood cancer departments in Denmark, Norway and Sweden identified 168 learning objectives in six categories: 1) acute life-threatening situations, 2) gastrointestinal side effects, 3) pain, 4) palliation, 5) play and activity, and 6) prescription and administration of medicine.

The learning objectives in the second category: gastrointestinal side effects will inform the case and the multiple-choice quiz that will be applied in this trial (see supplemental material for learning objectives).

This trial will focus solely on the second category as gastrointestinal side effects are frequent and potentially severe clinical problems in childhood cancer that involve multiple healthcare professionals.

The objective of this trial is to study the effect of interprofessional versus monoprofessional case-based learning (CBL) on healthcare professionals’ knowledge of gastrointestinal side effects and attitudes towards team collaboration.

The hypothesis is that interprofessional case-based learning (ICBL) will improve healthcare professionals’ knowledge of gastrointestinal side effects and attitudes towards team collaboration.

## Methods

### Trial design

In this randomised controlled trial, the experimental group are interprofessional groups receiving CBL on children and adolescents with cancer and gastrointestinal side effects. The control groups are monoprofessional groups of either nurses or doctors. See Fig. 1 for a flowchart with an overview of the phases in the randomised controlled trial. The two groups will be taught using the same case.

**Fig. 1 Fig1:**
[figure not shown]
Flowchart of the progress of the phases in the randomised controlled trial

### Setting and eligibility criteria

This randomised controlled trial will take place at Rigshospitalet, University of Copenhagen and include eligible healthcare professionals from four departments: inpatient department for children and adolescents with cancer; inpatient department for transplantation of children and adolescents with cancer; and two outpatient departments for children and adolescents with cancer (Fig. 2 provides an overview of eligible participants). Professionals employed elsewhere includes priests, pedagogues (pre-school teachers), physiotherapists, social workers, teachers, occupational therapists and dieticians.

**Fig. 2 Fig2:**
[figure not shown]
Occupational background of the participants

### Exclusion criteria

Staff managers and staff involved in organising the study will be excluded from the intervention.

### Participant withdrawal

Participants will be informed by the principal investigator that they can withdraw their consent and discontinue their participation at any time. If any data has already been obtained, participants will be asked to give permission to include their data.

### Recruitment

All eligible healthcare professionals will be informed individually or in groups about the trial (for information material, please contact the corresponding author). Participants will be encouraged by the head of departments to participate in the programme.

The participants in the experimental group will be randomised into six interprofessional teams. The computer-generated allocation sequence will be designed to ensure an adequate composition of health professionals resembling authentic clinical teams of 10–18 people. For example, four nurses, two doctors, one physiotherapist, one priest, one teacher, one social worker and one pharmacist.

The participants in the control group will be randomised into four monoprofessional groups comprised exclusively of nurses and three groups exclusively of doctors (See Fig. 2).

Two weeks to one month before the CBL session, the participants will receive an email with a link to the three questionnaires (AITCS, RIPLS and SAQ) generated in the secure web application REDCap [16]. A follow-up questionnaire will be sent to the participants 1-3 months after the intervention with a link to the same three questionnaires (see Fig. 3 for Timepoints of measurements).

**Fig. 3 Fig3:**
[figure not shown]
Timepoints of measurements

An MCQ will test the participants’ knowledge before and after the CBL (see an example of MCQ item in Table 5). It will consist of one best answer format with three options will be developed for this trial based on guidelines for designing and developing questionnaires [17, 18]. The items in the multiple-choice quiz will be based on content in national guidelines. The national guidelines will be distributed to the participants before the CBL session by email as course material and will be available online [19].

**Table 5 Tab5:** Example from MCQ and example from course evaluation

Lesley 11 years old is in the hospital school while waiting to the results on blood samples. With her she has her medication box from home. Suddenly Lesley has a bit of a stomach-ache and would like her pain killer that she can take when she needs it. She just does not remember what it looks like.				
Who should the teacher contact:				
1. The nurse from the outpatient clinic				
2. The doctor from the outpatient clinic				
3. Lesley’s mom				
The professional content of the course was overall (only one mark):				
Very poor	Poor	Acceptabel	Good	Very good
1	2	3	4	5

### Pilot testing

The case and the multiple-choice quiz will be pilot tested on a group of healthcare professionals that resemble the interprofessional group. The facilitators of the CBL will be two doctors and two nurses who work with education, supervision and introduction of experienced new staff from the paediatric oncology department. The multiple-choice quiz will be face- and content validated [18].

The participants will be asked whether they participated in any other childhood cancer CBL interventions between enrolment in the trial and answering the final questionnaires.

For exploratory analysis, the CBL sessions will be audio-recorded, and field notes will be taken focusing on the perceived dynamics and interactions in the room [20].

### Outcomes

For primary and secondary outcomes, we will use self-reported questionnaires, using a five-point Likert Scale. All scales are professionally translated and validated for a Danish context [21–23].

#### Primary outcome

Assessment of Interprofessional Team Collaboration Scale (AITCS) is a self-reported assessment of team collaboration for healthcare professionals [24]. We chose this instrument as it is one of the rare instruments that measure interprofessional team collaboration in qualified healthcare professionals. The Danish version is from 2011 and consists of three subscales; 1) Partnership/shared decision making (19 items), 2) Collaboration (11 items), 3) Coordination (7 items) [21, 22]. The items are distributed on a 5-point Likert scale, 5 = always, 4 = most of the time, 3 = occasionally, 2 = rarely, 1 = never). The difference will be measured on the overall scale.

#### Secondary outcomes

Readiness for Interprofessional Learning Scale (RIPLS) is a self-reported assessment of readiness of interprofessional learning [25]. We will use the Danish version of RIPLS with four subscales and 29 items distributed on a 5-point Likert scale, 5 = strongly agree, 4 = agree, 3 = neutral, 2 = disagree, 1 = strongly disagree). Items 10, 11 and 12 should be reversely coded [26]. The difference will be measured on the overall scale.

Also, a secondary outcome, Safety and Attitude Questionnaire (SAQ) is a self-reported assessment of attitude towards patient safety with 60 items to be rated on a 5-point Likert scale, 5 = Agree strongly, 4 = Agree slightly, 3 = Neutral, 2 = Disagree slightly, 1 = Disagree strongly). Items two and 11 are negatively worded [23, 27]. We will use the Danish version of SAQ [23].

The final secondary outcome is difference in knowledge evaluated using MCQ; evaluation of participants’ attitudes about the CBL sessions; qualitative content analysis on interactions between healthcare professionals during the CBL sessions.

### Data collection

This study is ongoing with recruitment starting in September 2019; intervention begins on February 25th to April 1st, 2020. Data collection ends approximately August 2020.

Figure 3 and Table 6 lists timepoint of measurement and collection of outcomes.

**Table 6 Tab6:** Collection of outcomes

Schedule	2–4 months before intervention	2 months before intervention	1–2 months before intervention	Intervention: Case-based learning	1–3 months after intervention
Information for all staff	Oral information at meetings and conferences about case-based learning	Written and oral information by individual email to all staff	Oral information for participants interested in randomisation		
Trial participants			Participants will be included consecutively.		
Trial participants			Pre AITCS Pre RIPLS Pre SAQ	MCQ on gastrointestinal side effects Course evaluation	Post AITCS Post RIPLS Post SAQ
Data collection on participants			Demographic data: sex, age, profession and years of work	Observations of interaction: who speaks, when and about what	

*AITCS* Assessment of Interprofessional Team Collaboration Scale, *MCQ* multiple-choice quiz, *RIPLS* Readiness for Interprofessional Learning Survey, *SAQ* Safety Attitude Questionnaire

### Sample size

Data on the effectiveness of interprofessional education for making the sample size calculation are sparse [21, 28–30]. We have chosen to calculate the required sample size based on previous interprofessional cluster randomised studies [21, 30].

We assume that the primary outcome will be normally distributed with a standard deviation of 20 points [30]. Using a t-test to compare the means in the experimental and the control group and assuming a mean difference of 12 [30], a power of 80% and a significance level of 5%, we need 45 participants in each group.

### Sample size estimation adjusted for clustering

Observations on participants on the same team will be correlated [31], which means the effective sample size will depend on the intraclass correlation coefficient (ICC) [31]. To adjust the sample size, the crude sample size needs to be multiplied by the design effect. The average cluster size is 13, and we assume the ICC to be 0.05.

Design effect =1 + (cluster size – 1) x ICC → design effect =1.6. Accordingly, the sample size will be 45 × 1.6 = 72 participants in each arm. With at least 80 participants in each group, there is room for up to 10% missingness.

### Statistical methods

We only expect a small number of missing observations (due to illness, rescheduling, absences) and will assume that these will be missing at random, [32] in which case the linear mixed model is valid, if correctly specified.

For all outcomes, the group means in the experimental and the control group postintervention will be compared, adjusting for the preintervention scores using a linear mixed model that includes the postintervention as outcomes, assuming the group means at baseline to be equal due to randomisation (a constrained linear mixed model [33]). Analyses will be performed unadjusted and adjusted for sex, age, profession and years of work.

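### The analysis section names no team term although the sample size assumes team correlation; run that way, the 5% test has about 12% type I error

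*Protocol article*

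**What the plan says.** The Abstract calls the study a "single-centre, investigator-initiated cluster randomised trial". Under Sample size estimation adjusted for clustering, the protocol article states: "Observations on participants on the same team will be correlated". It takes an average cluster size of 13 and an ICC of 0.05, obtains a design effect of 1.6, and raises the requirement from 45 to 72 per arm, with at least 80 planned to allow for missing data.

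Details of the intervention fixes the number of teams: six interprofessional teams in the experimental arm, and four nurse and three doctor groups in the control arm, 13 in all.

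Statistical methods describes one analysis for all outcomes. Post-intervention means are compared with adjustment for the earlier scores, "using a linear mixed model that includes the postintervention as outcomes, assuming the group means at baseline to be equal due to randomisation". The section labels this a constrained linear mixed model, assumes data missing at random, and plans one analysis without covariates and one adjusted for years of work, profession, age and sex. Neither team nor session is mentioned, and no random effect or covariance structure of any kind is given.

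**The concern.** The sample size section treats team correlation as a fact that inflates the variance of the group comparison by 60%. The analysis section gives the model class, baseline handling, missing-data assumption and covariates, but nothing that carries this correlation into the standard error. The features it does give (adjustment for the earlier score, equal baseline means, validity under missing at random) concern repeated scores on one person, not members of one session. An analyst who codes the section as written would fit a participant-level pre/post model.

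The profession covariate does not fill the gap. It cannot separate the four nurse sessions from one another, or the three doctor sessions, or the six mixed teams, and it is absent from the unadjusted analysis.

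At stake is the primary inference on AITCS. Without a team term the standard error is too small, the confidence interval too narrow and the false-positive rate above 5%. The extra 27 participants per arm recruited because of clustering would then be analysed as if there were none.

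A smaller point sits in the same sentence. Constraining baseline means to be equal requires the pre-intervention scores to be outcomes in the model, yet only the post-intervention scores are named as outcomes. The text can be read either as an analysis of covariance or as a constrained longitudinal model.

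**Working it through.** **Inputs from the protocol article.** Outcome "normally distributed with a standard deviation of 20 points"; "assuming a mean difference of 12"; "a power of 80% and a significance level of 5%, we need 45 participants in each group"; average cluster size 13; ICC 0.05; 6 + 7 = 13 teams. Sidedness is not stated; a two-sided test reproduces the stated number.

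**The plan's own figures.**
- Two-sided t-test with standardised difference 12/20 = 0.6: 44.6, rounded up to 45 per arm.
- Design effect (DE): 1 + (13 − 1) × 0.05 = 1.6.
- 45 × 1.6 = 72 per arm; 72/0.90 = 80 with 10% missing.

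The sample size reproduces and is not in error.

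**Type I error if team is left out.** The true variance of the difference is DE times the variance the model reports, so the true error of a nominal 5% test is 2·[1 − Φ(1.96/√DE)]. At cluster size 13:

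| ICC | DE | Type I error |
|---|---|---|
| 0.01 (assumed) | 1.12 | 0.064 |
| 0.02 (assumed) | 1.24 | 0.078 |
| 0.05 (protocol) | 1.60 | 0.121 |
| 0.10 (assumed) | 2.20 | 0.186 |

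**Effect of baseline adjustment.** Teams are formed after the baseline questionnaires, so the pre score can remove individual variance but not team variance. With pre-post correlation ρ, which the article does not give, the ICC after adjustment becomes 0.05/(1 − ρ²):
- ρ = 0.5: ICC 0.067, DE 1.80, type I error 0.144.
- ρ = 0.7: ICC 0.098, DE 2.18, type I error 0.184.

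**Simulation.** There were 6 and 7 teams, 80 per arm, ICC 0.05 and 8,000 trials under the null per setting. A regression of post score on group and pre score stood in for the participant-level model. The Monte Carlo standard error is about 0.4 percentage points.

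| Assumed ρ | Participant-level, baseline-adjusted | t-test on 13 adjusted team means, 11 df |
|---|---|---|
| 0 | 0.122 | 0.055 |
| 0.5 | 0.132 | 0.046 |
| 0.7 | 0.178 | 0.052 |

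Without baseline adjustment the participant-level test rejected in 11.0% to 12.3% of trials.

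**Power once team is respected.** The standard error is 20·√(2 × 1.6/n), and the reference is t on 13 − 2 = 11 df.
- n = 72: standard error 4.22, noncentrality 12/4.22 = 2.85, power 74% (normal approximation 81%).
- n = 80: standard error 4.00, noncentrality 3.00, power 78% (normal approximation 85%).

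These power figures take no credit for variance removed by the baseline score.

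**The case against.** The strongest reply is that silence is not exclusion. Statistical methods names no random effect at all, not even for participant. A linear mixed model can carry a team effect, and a random effect would not normally appear in a list of adjustment covariates. The article shows awareness of clustering in its Abstract and its sample size, and it makes the model's validity conditional on correct specification. It also condenses a fuller protocol, and an analysis plan that is not shown may hold the random-effects structure and the degrees-of-freedom method.

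Much of this stands. A reader might infer that the trial has decided to ignore clustering, or that the planned primary test runs at 12%. The document supports neither. The 12% requires that team is omitted and that the ICC is 0.05, which the article itself presents as an assumption; at 0.01 the error would be 6.4%. The baseline-adjusted figures rest on a correlation the article does not supply. Nor would it be right to infer that the sample size calculation is wrong.

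What does not stand is that this is merely detail left for later. The section goes as far as baseline constraint and covariates, and what it specifies does not match the premise on which the sample size was raised. By that premise, a model without team is not correctly specified. The outcome wording is a slip in a compressed sentence, since the intended method can be recognised, and is secondary.

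**Conclusion.** The point holds in conditional form. The protocol article relies on within-team correlation to set its sample size and describes an analysis with no team or session term. If that analysis is run as described, without team, the nominal 5% test has a type I error of about 12% at the protocol's own ICC and cluster size, with a range of about 8% to 19% over assumed ICCs of 0.02 to 0.10. It would be somewhat higher than 12% if baseline scores remove much individual variance: about 13% and 18% in simulation at assumed pre-post correlations of 0.5 and 0.7.

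These figures assume a common ICC in both arms, near-equal team sizes and a team effect on the post score only. If an unseen analysis plan already includes team, the inflation does not arise and the remaining task is to align the article's text with it. With only 13 teams, the reference distribution matters even then.

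**What to change.** Amend Statistical methods so that it:
- names both pre- and post-intervention scores as outcomes, as a constrained-baseline model requires;
- includes a random effect of team (session) on the post-intervention score;
- uses Kenward-Roger or Satterthwaite degrees of freedom for 13 teams, or replaces the model with an equivalent team-level analysis;
- applies this to AITCS, RIPLS, SAQ and the post-session MCQ.

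The team-level test is the version whose error rate was checked here (about 5%); the mixed model with small-sample degrees of freedom was not simulated.

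The change costs one paragraph and a few lines of code, and needs no new data beyond each participant's session. The price is wider confidence intervals and approximate power of 74% to 78% on 11 degrees of freedom, before any gain from baseline adjustment, against the 80% planned. The degrees-of-freedom method should be fixed before the data are analysed.
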